### Recruitment {15}

Patients are recruited from regular referrals to the NPI. As the NPI is part of Arkin, a large Mental Health Institute in Amsterdam, the central enrolment office of Arkin performs a triage based on information of referrers. If needed, additional screening by phone is conducted to select patients suitable for specialized care for personality pathology. Most patients have a history of unsuccessful therapies either for co-morbid disorders or for PD. The intake clinician at the NPI uses the SCID-5-P for obtaining a DSM-5 classification. In case of a diagnosis of a Cluster-C PD (avoidant, dependent or compulsive) or another specified personality disorder with predominantly Cluster-C traits, the patient receives both written and face-to-face information about FORCE and is motivated to participate by the intake clinician. If a patient is interested in participating in the study, a protocolized shared decision procedure is carried out to choose group or individual setting, with group therapy being the first choice. Contraindications for group therapy and/or a strong preference can lead to an indication for individual therapy. In this case, the patient will enrol in I-FORCE (Daniëls et al., in prep.). When a patient prefers to receive group therapy, referral to G-FORCE will follow (see Fig. 1 for an overview of the patient flow).

**Fig. 1 Fig1:**
[figure not shown]
Flow chart of the study design

### Who will take informed consent? {26a}

After referral to G-FORCE, the research assistant will inform the patient and re-check the eligibility. If eligibility is confirmed, the patient will be asked to sign the informed consent. The patient receives all the information about the trial 1 week before the eligibility screening, providing sufficient time for reflection.

### Additional consent provisions for collection and use of participant data and biological specimens {26b}

Not applicable.

## Assignment of interventions: allocation

### Sequence generation {16a}

After informed consent is signed and baseline measurements are completed, the patient is randomized to one of the three treatments. Randomization is stratified by type of Cluster-C PD (avoidant, dependent, obsessive–compulsive, otherwise specified) and location (Amsterdam or Amersfoort/Utrecht) and performed by a computerized randomization program.^5^

### Concealment mechanism {16b}

Allocation sequence is concealed, as randomisation is computer-generated and performed after the patient has signed the informed consent and after baseline assessments are completed.

### Implementation {16c}

The generation of the allocation sequence is done by an independent statistician, who allocates the patient to one of the treatments. The research assistant receives the information on the allocation from the independent statistician and informs the patient about which treatment has been assigned.

## Assignment of interventions: blinding

### Who will be blinded {17a}

Because the study is a clinical psychotherapy trial, it is not possible to blind therapists and participants. However, the research assistants who perform the baseline assessments will be blind for treatment allocation. Also, the other assessments that contain diagnostic interviews are conducted by blinded research assistant. In this way, knowledge about the type of treatment will not affect the outcome of the assessment.

### Procedure for unblinding if needed {17b}

Participants and therapist are not blinded; therefore, there is no procedure for unblinding.

## Data collection and management^6^

### Plans for assessment and collection of outcomes {18a}

Data will be derived from electronic patient records and collected with an electronic Case Report Form (eCRF) using Access. Patients will use an online survey (NetQ) to answer questionnaires. Interviews will be coded and results will be stored in NetQ. Audiotapes will be stored in MS Teams in a folder protected with a password. All data acquired during the study will be anonymized and saved in a study folder on our protected research server. Only the study team has access to this specific study folder.

### Plans to promote participant retention and complete follow-up {18b}

The patients will receive extensive information about the study set-up and requirements during the recruitment. The importance of completion of the follow-up will be stressed. Patients will receive a reimbursement of 20 euros after completing the assessment at 24 months and another 20 euros after completing the last assessment. Patients are allowed to stop at any time during the study and are not obliged to give a reason to discontinue. Questionnaires are completed using an online survey, and therefore patients can do this at any convenient moment, within a time frame of 2 weeks before or after the assessment time points. All patients are reminded throughout the study to fill out the questionnaires. Throughout the follow-up period, the researchers will check responses and if necessary, contact patients for completion of their follow-up.

### Data management {19}

Online Case Report Forms (CRF) are used online (digital platform NetQ), which will allow standardised data capture, as well as facilitate typing, versioning or uploading of documents. In addition, each assessment will have a standardised operational procedure (SOP) to increase internal consistency. Such SOPs will determine who may conduct the assessment (either online or face-to-face), evaluation steps and standardised communication with research participants.

### Confidentiality {27}

Research data will be stored using a study identification code for each participant. The key document will only be accessible to the principal investigators and the statistician of the mental health institute (Arkin) and will be safeguarded by the principal investigator according to research guidelines after completion of the study. Publications will only report aggregated statistical information, which cannot be related to individual participants.

### Plans for collection, laboratory evaluation and storage of biological specimens for genetic or molecular analysis in this trial/future use {33}

Not applicable.

## Statistical methods^7^

### Statistical methods for primary and secondary outcomes {20a}

#### Primary study parameter(s)

##### Treatment response: ADP-IV

All analyses will be conducted according to the intention-to-treat principle. Primary and secondary outcomes are analysed with Linear Mixed Models, with random effect of group if estimation allows. The primary outcome measure is the change in total score on the ADP-IV at 24 months using dimensional scoring algorithms [77]. Change in the primary outcome measure and the relative effectiveness of the three treatments will be analysed using mixed regression so that all available data are used, taking into account the levels of participant, time and group. The underlying distribution of the mixed regression model will be determined based on the distribution of residuals (e.g. normal, gamma, negative binomial). Per-protocol analyses will also be conducted to test for robustness.

Because of the dosage differences, an additional comparison of effectiveness will be conducted at the different end points of the treatments (resp. 12, 18 and 24 months).

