### Objectives {7}

The aim of this pragmatic randomized clinical trial is to compare the effectiveness and cost-effectiveness of three group therapy formats that are regularly delivered in clinical practice to patients with a Cluster-C PD in a superiority study design. The primary outcome is the severity of the Cluster C-PD. The slopes over time of the three treatments (GST-C, SFGT and PG) from baseline to 24 months will be compared. Because of the variable durations of the treatments, we will make a comparison over a time window of 24 months, with assessments taking place at baseline, 3, 6 and 9 months, and at the different end points of the treatments at 12, 18 and 24 months, respectively. Next to the a priori tests over 24 months, we will explore differences between the outcomes of the three treatments on the slopes over time between start of treatment and the respective (different) end points. Differences in outcome at 36 months follow-up will be studied separately. No hypothesis was formulated about the direction of the difference.

The second aim is to study potential mechanisms of change both across therapies and for each specific theoretical framework by determining mediators in repeated measurements during and after therapy, across treatment conditions [58]. Group cohesion, group climate and working alliance are chosen as hypothesized general working mechanisms for group therapy. Another focus of research is the relationship between specific treatment interventions, mediators and outcome. The hypothesis is that certain interventions will be stronger connected to mediators and outcome than others. For example, we expect group dynamic interventions to be positively related to group cohesion.

The third aim is to study potential predictors and its moderating impact on outcome. The hypothesis is that for patients with higher levels of childhood trauma, schema therapy will be more effective, because of its use of trauma-oriented techniques, such as imaginary rescripting [34, 74]. Another hypothesis is that a more structured therapy such as GST-C will yield better results for patients with more severe personality pathology, e.g. borderline personality organization [54]. These patients are less able to tolerate high anxiety levels which can be provoked by the unstructured and exploratory character of PG [39]. Autism traits and vulnerable narcissism will be studied exploratively.

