### Outcomes {12}^2^

Baseline assessment takes place right after informed consent and before randomization and start of treatment. Assessments consist of digital questionnaires and semi-structured interviews and are all administered in Dutch. Assessors are trained and will be supervised to ensure quality of data collection of semi-structured interviews. Table 1 shows an overview of the instruments per assessment point.

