### Sample size {14}^3^

First, the required sample size was calculated to compare the three types of active treatments. Three pairwise comparisons will be conducted between the active treatment arms (PG vs. SFGT, PG vs. GST; SFGT vs. GST). To detect a medium effect size (*f* = 0.11) in a pairwise comparison of pre-post change between two active treatment arms, with *f*(*v*) = 0.2460 and Cohens *d* = 0.492, with Bonferroni-corrected alpha = 0.0167, a power of 0.80 and within-person correlation coefficient = 0.60, 88 patients are needed per arm. Because three types of therapies will be compared, 3 × 88 = 264 participants are needed to perform three pairwise comparisons. A medium effect size (*f* = 0.11^4^) is chosen to detect a clinically meaningful difference, as opposed to a smaller effect size. The correlation of 0.60 is an educated guess of the correlation between repeated assessments based on the previous RCTs the authors conducted.

The final analysis will be conducted with mixed regression on time series: the change in slope over time between two treatments. Because power analysis for mixed regression is complex and based on complex assumptions about the covariance-structure, a simplified approach was chosen by conducting a power analysis on the pre-post change.

In this study, we must take into account the correlation of observations within group psychotherapy, with an assumed Intra Class Correlation of 0.1. ([88], page 186). Therefore, we will increase the needed numbers with 10%, resulting in a total of 290 participants.

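### The therapy-group random effect is kept only on condition that it can be estimated, with no fallback that retains clustering; if it is lost, or is only a time-constant intercept on a slope contrast, each 1.67% test runs at about 4-9% for 5-9 trial patients per group

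*Protocol article*

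**What the plan says.** The section on treatment response (ADP-IV) in the protocol article sets the model: "Primary and secondary outcomes are analysed with Linear Mixed Models, with random effect of group if estimation allows". It does not say whether the group effect is an intercept or varies with time, nor what is fitted if it cannot be estimated. Shortly afterwards the same section describes the mixed regression as "taking into account the levels of participant, time and group", this time without a condition.

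Sample size {14} is firm that "we must take into account the correlation of observations within group psychotherapy", and assumes an ICC of 0.1.

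The primary contrast is a difference in slopes. Objectives {7}: "The slopes over time of the three treatments (GST-C, SFGT and PG) from baseline to 24 months will be compared". Sample size {14}: "The final analysis will be conducted with mixed regression on time series: the change in slope over time between two treatments". The treatment response section, however, also describes the primary outcome as change in the ADP-IV total at 24 months.

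Outcomes {12} fixes the timing of baseline: "Baseline assessment takes place right after informed consent and before randomization and start of treatment".

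**The concern.** There are two ways in which the tests could lose their error control.

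**Omission.** The plan expects patients in the same therapy group to be correlated, yet allows the term that represents this to be left out, with nothing put in its place. The standard error of a treatment comparison is then too small. The increase in sample size for clustering does not help: more patients do not repair a standard error computed as if they were independent.

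**Form.** Patients are randomised individually and baseline precedes randomisation, so no therapy-group effect exists at baseline. It can only develop during treatment, as groups diverge over time. A group intercept that is constant over time cancels from a within-patient slope or change, so it leaves the treatment-by-time standard error uncorrected.

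At stake are the three Bonferroni-corrected primary comparisons and the secondary outcomes analysed the same way. Variation between therapy groups, including that due to their therapists, could be reported as a difference between therapies.

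**Working it through.** **Inputs from the protocol article**
- Sample size {14}: "with Bonferroni-corrected alpha = 0.0167, a power of 0.80 and within-person correlation coefficient = 0.60, 88 patients are needed per arm"; f = 0.11; ICC 0.1, without saying whether it applies to the score or to change; total 290 after a 10% increase, about 97 per arm.
- Two-sided testing is inferred from Objectives {7}: "No hypothesis was formulated about the direction of the difference".
- Intervention description {11a}: at most 9 participants per group in GST-C and PG, with rolling entry; no maximum stated for SFGT.
- Assumed: m = 5 to 9 trial patients per group. The upper end is the stated maximum. The lower end is borrowed from the group-size range that the background cites for cohesion, which is not a design figure.

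**Step 1: the plan's own figure reproduces.** f(V) = 0.11 × √(2/(1 − 0.60)) = 0.2460, and d = 2 × 0.2460 = 0.492. With the noncentral t, power is 0.7952 at 87 per arm and 0.8005 at 88. Then 3 × 88 = 264, and 264 × 1.10 = 290.4.

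**Step 2: true error if group is ignored.** With DE = 1 + (m − 1) × ICC and z = 2.393 for two-sided 0.0167, true α = 2 × [1 − Φ(z/√DE)]. If the ICC of 0.1 refers to the 24-month score, then on unit variances change has variance 2 × (1 − 0.60) = 0.8, and the ICC of change is 0.1/0.8 = 0.125.

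| m | DE (ICC 0.1 on change) | True α | DE (ICC 0.125 on change) | True α |
|---|---|---|---|---|
| 5 | 1.40 | 4.3% | 1.50 | 5.1% |
| 7 | 1.60 | 5.9% | 1.75 | 7.0% |
| 9 | 1.80 | 7.4% | 2.00 | 9.1% |

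With ICC 0.05 and m = 9, DE is again 1.40 and α is 4.3%. A change-score simulation at ICC 0.1 and 0.125 (20,000 replicates, about 97 per arm) agreed with the table. It put the family-wise error over three pairs at 10.6-12.4% (m = 5), 14-17% (m = 7) and 17-21% (m = 9), against 5%.

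**Step 3: does a group intercept help on a slope contrast?** Data were simulated at 0, 3, 6, 9, 12, 18 and 24 months with group effects growing from zero at baseline, and REML mixed models were fitted (600 replicates per setting). Each range covers the two ICC scales.

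| Group term in model | m = 5 | m = 9 |
|---|---|---|
| None | 4.5-4.8% | 9.7-11.5% |
| Intercept only | 4.5-4.8% (identical) | 9.7-11.5% (identical) |
| Intercept and slope, z reference | 1.7-1.8% | 2.0-2.8% |
| Intercept and slope, t with group-level df | 1.2-1.3% | 1.0-1.7% |

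The Monte Carlo standard error near 10% is √(0.1 × 0.9/600) = 1.2 percentage points. The intercept changed nothing; the random slope with group-level df brought the error to nominal or just below.

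**Step 4: what if the term is dropped only when its variance estimate is zero or below?** In 40,000 simulated trials per setting at ICC 0.1, this happened in 2.7% (m = 5), 1.6% (m = 7) and 1.3% (m = 9). Overall error under that rule was 1.6-1.7%, which is nominal.

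**The case against.** Four points can fairly be made on the other side.

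1. A reader might infer that the plan specifies an intercept-only group effect. It does not. It names a random effect of group without giving its form, and the second sentence refers to participant, time and group levels. If 24-month change is the dependent variable, as one sentence suggests, a group intercept acts on change and does correct the contrast. The exact form and the degrees-of-freedom method are also details that an analysis plan, not shown here, may settle. This stands: the intercept argument is conditional.

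2. A reader might infer that the group effect will probably be dropped. The document does not support that. It gives no number of groups, and at the plan's ICC a zero variance estimate is rare (Step 4). This stands too. But the condition as written is not limited to that harmless case. It also covers non-convergence, and the section leaves open gamma or negative binomial models, which can be harder to fit.

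3. A reader might take 7-9% as the typical error. That needs 9 trial patients in every group, a stated maximum for two arms only. Smaller groups give less. Rolling entry could put more than 9 trial patients through one group over time, although those who never overlap may be less correlated. Cluster size is therefore uncertain in both directions.

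4. A rule that the group term may never be removed would go further than error control requires, since removing a component estimated at zero leaves the error nominal.

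None of this removes the stated condition, the missing fallback, or the conflict with the unconditional sentence and the assumed ICC.

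**Conclusion.** The concern holds in limited form. The protocol makes the group effect conditional, names no substitute, and contradicts both its own unconditional sentence and its assumption of within-group correlation.

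If group is omitted for a reason such as non-convergence, or modelled only as a time-constant intercept on a slope contrast, each test at nominal 1.67% runs at about 4-9%. This assumes ICC 0.1, 5 to 9 trial patients per group, about 97 patients per arm and two-sided tests. About 7-9% applies only to full groups of 9; there the simulated multi-visit slope test was somewhat higher, at 9.7-11.5%. Even the low end is about 2.6 times nominal (4.3/1.67).

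The documents do not show that such an omission is likely, or that an intercept-only model is intended. The inflation does not arise when the term is dropped solely because its variance is estimated at zero.

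**What to change.** Before the analysis, reconcile the two sentences in the treatment response section and replace the open condition with a rule:

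- Prespecify a therapy-group random effect on post-baseline change: group-by-time (zero at baseline) if slopes are modelled, or a group intercept if change is the dependent variable. State which dependent variable is used.
- Use Kenward-Roger or Satterthwaite degrees of freedom, so that inference reflects the number of groups.
- On non-convergence, simplify the participant-level covariance first, or use small-sample-corrected cluster-robust standard errors by therapy group, so that clustering is not discarded. A variance component estimated at zero may be treated as zero.

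The cost is wording in the protocol or analysis plan. The downside is wider, but correct, confidence intervals.

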##### Differential treatment response

To gain more insight into differential treatment response, we will first examine which of the potential predictors actually predict (differential) treatment response. In the moderator analyses, we will utilize the Personalized Advantage Index (PAI) analysis developed by DeRubeis [24], previously used in the research group of the principal investigator [15, 16]. In step 1, four univariate regression models will be built for each specific predictor, with the predictor and separate variables for the interaction with the three interventions (moderators). In step 2, a multivariable regression model with the significant predictors (and their interaction with treatment) from step 1 will be developed, to examine the relative contribution of each potential predictor or moderator. The outcome variable is the ADP-IV. In addition, we will make use of a data-driven approach, in which machine learning techniques are used to select the moderators to be added into the PAI algorithm.

##### Mechanisms of change

It is hypothesized that the interventions exert a positive effect on the severity of Cluster-C manifestations measured by the ADP-IV, through their impact on the underlying general and theory specific mechanisms of change. To identify non-specific and specific mechanisms of change and the strength of the factors involved, both multilevel mediation models and structural equation models will be used. These analyses are based on the Latent Change Score models for mediation used in the research group of the principal investigator [15, 16].

#### Secondary study parameters

##### (Differential) treatment response: secondary study parameters

Mixed regression analysis is used to examine change on the secondary outcome measures in the three treatments. The secondary outcome measures include severity of cluster C PD, reliable change and recovery, personality functioning, general functioning, general psychopathology, quality of life and happiness. As the PD-severity indices AVPDSI, DPDSI and OCPDS vary per primary PD, they will be first standardized before they are analysed in the complete sample. This analysis will be controlled for primary PD, to account for possible differences in sensitivity to change. The underlying distribution of the mixed regression model will be determined based on the variable type (scale, nominal) and the distribution of residuals (e.g. normal, gamma, negative binomial). In addition, preliminary analyses will test differential treatment retention using survival analysis and mixed logistic regression. Medication confounds will be examined.

##### Cost-effectiveness

The cost-effectiveness analysis (CEA) will be conducted from a societal perspective. Within the CEA, the difference in societal costs (measured by the TiC-P FORCE at baseline and after 6, 12, 18, 24 and 36 months) generated by patients in the three conditions will be related to the difference in clinical effects (measured with the ADP-IV and quality-adjusted life-years (QALYs) based on the EQ-5D-5L) over the course of 36 months. Missing cost and effect data will be imputed using multiple imputation. Mixed model regression analyses will be used to estimate cost and effect differences between groups. Bootstrapping with 5000 replications will be used to estimate 95% confidence intervals around cost differences and the uncertainty surrounding the incremental cost-effectiveness ratios (ICERs). Uncertainty surrounding the ICERs will be graphically presented on cost-effectiveness planes. Cost-effectiveness acceptability curves [32] will also be estimated. Adjustment for confounders and effect modifiers will be done if necessary.

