**Methods:**

In this mono-centre pragmatic randomized clinical trial, 290 patients with Cluster-C PDs or other specified PD with predominantly Cluster-C traits, will be randomized to one of three treatment conditions: group schema therapy for Cluster-C (GST-C, 1 year), schema-focused group therapy (SFGT, 1.5 year) or psychodynamic group therapy (PG, 2 years). Randomization will be pre-stratified on the type of PD. Change in severity of PD (APD-IV) over 24 months will be the primary outcome measure. Secondary outcome measures are personality functioning, psychiatric symptoms and quality of life. Potential predictors and mediators are selected and measured repeatedly. Also, a cost-effectiveness study will be performed, primarily based on a societal perspective, using both clinical effects and quality-adjusted life years. The time-points of assessment are at baseline, start of treatment and after 1, 3, 6, 9, 12, 18, 24 and 36 months.

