#### Provisions for post-trial care {30}

After termination of the treatment, a period of 6 months without psychotherapy is strongly advised. If for any reason additional care is necessary before these 6 months, the patient can reapply for therapy at the NPI, with a referral by the GP. In this case of reapplication, the research committee must be informed and can be involved in the decision making about the following therapy. If the patient reapplies after 6 months, but before the follow-up measurements are conducted, the same procedure is applicable.

No risk of harm is expected by participating in this trial.

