##### Costs

Costs are assessed using a specifically adapted version of the TiC-P [93]. The TiC-P FORCE is a 14-item self-report questionnaire to assess health care costs (part I) and costs resulting from productivity losses (part II) associated with psychiatric disorders. In part I, the number of contacts with different health care providers over the last 6 months is assessed. Part II consists of items regarding absenteeism from paid and unpaid work and presenteeism (i.e. reduced productivity while at work) in the last 6 months.

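### The 36-month cost comparison relies on a 6-month-recall questionnaire whose schedule leaves months 24 to 30 uncovered for every patient

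*Protocol article*

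**What the plan says.** The Cost-effectiveness section of the Protocol article takes a societal perspective. It relates cost differences between the three arms to differences in effect "over the course of 36 months". Its cost source is the TiC-P FORCE, "measured by the TiC-P FORCE at baseline and after 6, 12, 18, 24 and 36 months". Missing costs and effects are to be multiply imputed, cost differences estimated by mixed models, and uncertainty obtained by bootstrapping.

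The Costs section fixes the recall period. In part I, "the number of contacts with different health care providers over the last 6 months is assessed". Part II covers absence from paid and unpaid work and "presenteeism (i.e. reduced productivity while at work) in the last 6 months".

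The abstract's Methods paragraph lists every assessment in the trial, with none at month 30: "The time-points of assessment are at baseline, start of treatment and after 1, 3, 6, 9, 12, 18, 24 and 36 months". It also gives the treatment lengths as 1 year for GST-C, 1.5 years for SFGT and 2 years for PG. Under Provisions for post-trial care, once therapy ends "a period of 6 months without psychotherapy is strongly advised", although patients may reapply before or after that period.

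**The concern.** Cost is a flow: a period that no form asks about contributes no information. Up to month 24 the form is given every 6 months and the windows join. After that the interval between forms doubles to 12 months while the recall stays at 6, so the schedule does not support the horizon that the analysis claims.

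The effect side is less exposed, because a utility score is a state and can be interpolated between two visits.

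The gap lies wholly in the follow-up period. The Limitations section gives cost-effectiveness at follow-up particular weight because the three therapies differ in dose. The arms are also at different distances from the end of their therapy when the gap occurs, so whatever is assumed about it may affect the arms unequally.

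**Working it through.** **Inputs.** Forms at t = 6, 12, 18, 24 and 36 months (Cost-effectiveness); recall of 6 months for both parts (Costs); horizon of 36 months (Cost-effectiveness); nominal treatment ends at months 12, 18 and 24 (abstract); an advised therapy-free period of 6 months after treatment (Provisions for post-trial care). The baseline form looks back before month 0 and adds nothing to the horizon.

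**Coverage.** Each form covers the interval from t − 6 to t.
- Forms at 6, 12, 18 and 24 cover 0–6, 6–12, 12–18 and 18–24, which join to give months 0–24.
- The form at 36 covers months 30–36.
- Total: 24 + 6 = 30 months, against a stated horizon of 36.
- Uncovered: months 24–30. This is 6/36 = 16.7% of the horizon and 6/12 = 50% of the time after month 24.

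**Position of the gap by arm**, taking month 0 as about the start of treatment:

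| Arm | Treatment ends | Gap, months after end | Share of post-treatment time uncovered | Advised therapy-free months |
|---|---|---|---|---|
| GST-C | 12 | 12–18 | 6/24 = 25% | 12–18 (covered) |
| SFGT | 18 | 6–12 | 6/18 = 33% | 18–24 (covered) |
| PG | 24 | 0–6 | 6/12 = 50% | 24–30 (not covered) |

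**Imputation.** Multiple imputation predicts a missing value from patients in whom it was observed. For months 24–30 there are none in any arm, so any value would come from an assumption. Bootstrapping the analysis would not carry the uncertainty in that assumption.

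**Illustration only.** Suppose re-treatment costs X per patient per half-year outside the advised therapy-free period and 0 inside it. X is an assumption; the documents give no cost figures.
- True cost in months 24–36: PG 0 + X = X; GST-C or SFGT X + X = 2X. True PG increment: X − 2X = −X.
- Doubling months 30–36: PG 2X, comparator 2X. Estimated increment 0, bias 0 − (−X) = +X.
- Counting the gap as zero: PG X, comparator X. Estimated increment 0, bias again +X.

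The two simplest ways of filling the gap err by the same amount in the same direction here, so a sensitivity analysis comparing them would show agreement and miss the error.

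**After the fix.** Adding a form at month 30, or a 12-month recall at month 36, gives 36 of 36 months.

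**The case against.** **The article is condensed.** How to interpolate over an interval is commonly left to a statistical or health-economic analysis plan, and the absence of such a rule here is not a fault. That stands. But instrument, recall and schedule are all fixed in this document, and no later plan can supply answers that were not collected. Table 1 is not shown, but the text on timing is explicit and consistent.

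**Other sources exist.** A reader might infer that costs in months 24–30 are never measured at all. The documents do not support that. The data collection section says data also come from electronic patient records, and the research committee must be told when a patient reapplies to the institute. Some re-treatment may therefore be traceable. Such records would not cover care elsewhere or lost productivity, which a societal perspective needs, and the Cost-effectiveness section names only the questionnaire.

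**The direction of bias is unknown.** A reader might also infer that the gap demonstrably biases the comparison against PG. The documents do not support that either. The therapy-free period is advice, early reapplication is allowed, and the advice concerns psychotherapy, whereas the costs include other care, absenteeism and presenteeism. Nothing says that these follow the same window. The illustration shows what could happen under one simple assumption and estimates nothing.

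**Reach.** The primary ADP-IV comparison and the costs of months 0–24 are unaffected.

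**Conclusion.** The concern holds as a coverage gap. The named cost instrument covers 30 of the 36 months over which costs are to be compared, and the missing half-year is the same for every patient. This follows from the stated recall and schedule without further assumption.

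That the gap sits in a different post-treatment phase in each arm rests on nominal treatment lengths and on month 0 being about the start of treatment. If the clock runs from baseline and patients wait before starting, part of PG treatment itself could fall in the gap. On either reading the gap need not be neutral between arms; its effect on the incremental costs cannot be sized or signed from the documents. It is a defect in a secondary analysis, but one that the protocol itself treats as important, and it should be corrected.

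**What to change.** Do one of the following, in the same way for all arms:

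1. Give the 14-item TiC-P FORCE online at month 30.
2. Have the month-36 form ask about the last 12 months in two half-year blocks for all patients.

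With either, take institute contacts for months 24–30 from the electronic patient records, noting that these do not cover outside care or productivity losses. For patients already past these points, state the interpolation used and vary it in sensitivity analyses that go beyond comparing doubling with zero.

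The change was still practicable at submission: 167 of the planned 290 patients had been included, leaving 290 − 167 = 123 to enrol.

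The cost is one extra short online form, or somewhat more recall error with the 12-month recall. Shortening the base case to 24 months needs no new data, but I would not recommend it: it would count all of PG's treatment and none of its post-treatment period, against about 12 post-treatment months for GST-C.
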